### Sample size

As stated in the Introduction, only 10-15% of T2DM patients achieve all three treatment targets for both HbA1c, lipids and blood pressure. We estimate the percentage of patients that already has reached three targets at the start of the study will be approximately 10%. We hypothesise that in the OPTIMAL study, after two years of follow-up, the intervention group will show an increase of this percentage until 30% (about 10% increase per year), whereas in the treatment-as-before-group this percentage will stay at 10%. Assuming a two-sided significance level of 5%, with alpha 0.05 and power of 80% and with a drop-out of 10%, 65 patients will be needed in each treatment group (Department of Statistics Sample Size Calculator, University of British Columbia). Because the OPTIMAL study is a cluster randomised study the sample size will require an correction for the cluster effect. The used correction factor is equal to [1 + (m - 1) r], where ‘m’ is the total amount of eligible patient per practice (approximately 6), and ‘r’ the within-cluster correlation coefficient. For ‘r’ we use a within-cluster correlation coefficient of 0.025, based on the cluster correlation found in the ADDITION-Europe study. When taken the cluster effect (1.125) in to account, 73 patients per group are needed.

### Statistical analyses

Intention-to-treat analyses (ITT) will be performed to examine between-group differences. Generalized linear models will be used to correct for clustering at practice level. The proportions of achieved treatment goals of HbA1c, blood pressure, LDL-cholesterol within each study group will be estimated by calculating relative risk. The same applies to the difference between groups in the proportion of patients which achieved all the five above mentioned treatment goals. A p-value of <0.05 is considered statistically significant. To identify patients who show better results after the SDM process, the analysis for the primary outcome will be repeated with taken into account interaction of SDM with age, gender, education level, duration of diabetes and comorbidities. Within and between group differences in treatment satisfaction, perceived quality of life, health status, well-being, and coping style between baseline and 24 months follow-up will be analysed by using paired t-tests and mixed models respectively. We will add random effects for patient and practice.

The SDM-Q9 will be analysed in the intervention group by using paired t-tests. Mixed models will be used to study the between groups differences after 24 months. We will add random effects for patient and practice.

To evaluate the SDM proces, the tapes will be evaluated by two independent observers by making use of the SDM-Q9.

The Medical Research Ethics Committee of the University Medical Centre Utrecht has approved the study protocol (Protocol number: 11-153).

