In a recent statement of both the American Diabetes Association (ADA) and the European Association for the Study of Diabetes (EASD) personalised and patient-centred care is mentioned as the cornerstone of the treatment of patients with T2DM. The use of a decision support tool is strongly advocated [8]. A decision support tool can encourage active patient participation in many evidence-based healthcare decisions [20-22]. In the last decade decision support tools have been developed to support the achievement of cardiometabolic goals and to select patient-centred treatment options for lifestyle modifications or medication use [8,23-28]. However, most of them focus on a single risk factor [25], on only the patients’ preferences [26,27] or on some individual clinical characteristics [28]. We hypothesise that a decision support tool that takes into account both treatment intensity, patient’s clinical characteristics and patient’s preferences can facilitate a SDM process and will be effective in achieving treatment targets. We aim to evaluate whether such an approach increases the proportion of treatment targets that T2DM patients achieve.

The following research questions are addressed:What is the effect of shared decision making with a multi-faceted decision support tool on the percentage of patients with T2DM that achieve all individualised treatment targets for HbA1c, blood pressure and LDL-cholesterol; and to identify determinants for achieving all individualised treatment targets.What is the effect of shared decision making with a multi-faceted decision support tool on treatment satisfaction, quality of life, health status, well-being and on coping styles?What is the level of SDM-knowledge/attitude of the GPs from both treatment groups after 24 months?

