### Outcome measures

Primary outcome will be the proportion of patients that achieve all the three treatment goals for HbA1c, blood pressure, and total cholesterol .In addition to identify determinants of better performing patients for the primary outcome will be performed taken into account the interaction of SDM with age, gender, education level, duration of diabetes and comorbidities.

Secondary outcomes:The proportion of patients that achieve the all five treatment goals for HbA1c, blood pressure, total and LDL- cholesterol, body weight, and smoking.The following patient reported outcomes: diabetes treatment satisfaction, perceived quality of life, health status, well-being, and coping style.A process evaluation of the shared decision making ability of the general practitioners during the complete study. Outcome on GP level: the level of SDM-knowledge/attitude.

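### Research question 1 asks for determinants of achieving all targets, but the only analysis stated for it tests SDM-by-factor interactions, which address who responds better to SDM

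*Protocol article*

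**What the plan says.** The aim appears in three places in the protocol article, and its meaning shifts between them.

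- **Background, research question 1.** After asking for the effect of SDM on the percentage reaching all targets, the question adds "to identify determinants for achieving all individualised treatment targets". This clause does not mention a differential response to SDM.
- **Outcome measures.** The same word returns, now tied to interaction: "In addition to identify determinants of better performing patients for the primary outcome will be performed taken into account the interaction of SDM with age," followed by gender, education level, duration of diabetes and comorbidities.
- **Statistical analyses.** The purpose is put as "To identify patients who show better results after the SDM process", and the method is that "the analysis for the primary outcome will be repeated with taken into account interaction of SDM with age, gender, education level"; the list there also names diabetes duration and comorbidity.

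The surrounding text in Statistical analyses fixes the rest of the setting. "Generalized linear models will be used to correct for clustering at practice level"; goal achievement "will be estimated by calculating relative risk"; and "A p-value of <0.05 is considered statistically significant". Nowhere does the article state an analysis of the association between any of the five factors and reaching all targets.

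**The concern.** Two different questions share the word determinant.

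- **Prognostic question (Background):** is the factor related to reaching all targets? The null is no association between factor and success.
- **Effect-modification question (Statistical analyses):** does the SDM effect differ across levels of the factor? The null is an equal SDM effect at every level.

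A factor with the same strong effect in both arms violates the first null and satisfies the second. If determinants are read from the interaction term, as the Outcome measures wording suggests, such a factor would usually go unreported. Conversely, a significant interaction could be presented as a determinant of success when it shows only that SDM works differently in that subgroup. This is about which hypothesis is tested, and is separate from how many interactions are tested or how many false positives they produce.

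**Working it through.** **1. Inputs from the Sample size section.** Success 10% in control and 30% with SDM; two-sided 5%; 80% power; 10% dropout; about 6 patients per practice; within-practice correlation 0.025; 73 per group.

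**2. The plan's own figure.** With unpooled variance, n = (1.960 + 0.842)² × (0.10×0.90 + 0.30×0.70) / 0.20² = 58.9, so 59 per arm. Then 59 × 1.1 = 65. The design effect is 1 + (6 − 1) × 0.025 = 1.125, and 65 × 1.125 = 73.1. The stated 65 and 73 reproduce. The effective size left for analysis is 73 × 0.9 / 1.125 = 58.4, or about 58 per arm.

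**3. An exact example.** Assume (the documents give neither figure) a binary factor in 50% of patients with the same relative risk (RR) of 3 in both arms. To keep the arm averages at 10% and 30%, the risk without the factor is 2 × 0.10 / (1 + 3) = 0.05 in control and 2 × 0.30 / (1 + 3) = 0.15 with SDM.

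| | Control | SDM | RR of SDM |
|---|---|---|---|
| Factor absent | 0.05 | 0.15 | 3.0 |
| Factor present | 0.15 | 0.45 | 3.0 |

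The factor triples success, yet the SDM relative risk is 3.0 in both rows. The interaction null is exactly true on this scale, so a larger trial would not help.

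**4. Dependence on scale.** In the same table the SDM odds ratios are (0.15/0.85)/(0.05/0.95) = 3.35 and (0.45/0.55)/(0.15/0.85) = 4.64, and the risk differences are 0.10 and 0.30. Those scales do show some interaction, but it is still effect modification and not the factor's own association with success.

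**5. Simulation.** Trials were simulated with these arm rates, 50% prevalence and an equal RR in both arms, and analysed by Poisson regression with robust variance at two-sided 5%. Trials with an empty event cell count as non-rejections for the interaction model. Patients are treated as independent; the 58-per-arm column stands in for dropout and clustering.

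| Test, common RR 2 to 3 | 73 per arm | Effective 58 per arm |
|---|---|---|
| Pooled main effect (arm + factor) | about 52-88% | about 41-79% |
| Interaction | about 2% | about 2% |

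At RR 1 the pooled test rejects in 4.8% at 73 per arm, so its advantage is not an inflated error rate. A simpler cell-based Wald calculation gives 47% (RR 2) and 84% (RR 3) at 73 per arm and 33% and 71% at 58, again against about 2-3% for interaction.

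For a weaker factor, RR 1.5, the pooled test rejects in about 23% at 73 per arm and about 17% at 58, so the gap at 58 is only about 15 points.

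**6. The factor's own term in the interaction model.** With 0/1 arm coding this term is the factor's effect in controls only, where 73 × 0.10 = 7.3 successes are expected. At 73 per arm and RR 2 to 3 it rejects in about 4-7%. With the arm centred it becomes an average over the two arms and rejects in about 28-54%. The article states no coding and does not say that this term will be reported.

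**The case against.** The strongest reply is that Statistical analyses states its own aim, finding patients who do better after SDM, and that interaction is the standard analysis for that. Outcome measures also links determinants to interaction, so the clause in research question 1 may just be loosely worded. This stands in part: the interactions suit the aim stated beside them and should stay. But the research question as printed is broader, and on this reading it needs rewording. Either way the sections must be reconciled.

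A second reply is that a condensed article need not list every exploratory model. That would be decisive if the article were silent. It is not silent: it states the question and names one analysis for it, and that analysis has a different null.

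A reader might also infer that the trial cannot answer the question, or that no prognostic factor will be found. The text does not support either. It does not say that determinants are read only from the interaction coefficient; centred coding would recover part of the information; and a prognostic model could be run later on the same data.

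Finally, the roughly 2% rejection rate follows from assuming equal relative risks, so it illustrates the mismatch and does not predict the result. The 73 per arm already includes allowances for dropout and clustering, so the figures at 58 are the fairer guide.

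**Conclusion.** The mismatch holds. Research question 1 asks for determinants of reaching all targets, and the only analysis stated for that aim addresses effect modification. For a factor with a common RR of 2 to 3, the difference between the analysis that fits the question and the one stated is about 41-79% against 2% at an effective 58 per arm, and about 52-88% against 2% at 73. These figures rest on an assumed 50% prevalence, equal relative risks in both arms, the relative-risk scale and the plan's 10% and 30% success rates. For weaker factors the gap is much smaller. The aim is exploratory, and the primary comparison and sample size are not touched. It is worth correcting, but no threat to the trial's main conclusion.

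**What to change.** In Statistical analyses, add for the determinants question an exploratory pooled model of the primary outcome with arm plus the main effect of each listed factor. Fit one factor at a time without an interaction term, use the same practice-level clustering correction, and report relative risks with 95% confidence intervals. Keep the SDM interactions for the separate question of who benefits more from SDM. Reword research question 1 and Outcome measures so that determinant means a factor associated with success and effect modifier means a factor that changes the SDM effect.

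The cost is five simple models on variables that Measurements, data collection already lists, plus wording. The downside is a few more exploratory estimates, to be labelled as such.

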**Flow chart.**

### Practices and patients

Eligible GPs are those who included at least included one patient in the ADDITION-study. For the OPTIMAL study each GP should include at least two more or less comparable patients: 1. Former ‘ADDITION’ patients diagnosed with T2DM in 2002-2004 by screening, aged between 50-70 years at that time and having participated in the ADDITION study that ended in 2009; 2. Patients between 60 and 80 years in 2012-2014, known with type 2 diabetes for 8-12 years but not diagnosed in the ADDITION study. Patients will be excluded if they have a history of alcoholism, drug abuse, psychosis, personality disorder or another emotional, psychological or intellectual problem that is likely to invalidate informed consent, or limit the ability of the individual to comply with the protocol requirements. Also, patients with a limited life expectancy will not be approached.

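### The search for who benefits from SDM tests five interactions at p<0.05 on about 26 expected events; it should be declared exploratory and reported as estimates with intervals

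*Protocol article*

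**What the plan says.** Three sections of the protocol article deal with the search.

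- **Background, research questions.** Question 1 asks for the effect of SDM on the share of patients reaching all targets, and also undertakes to "identify determinants for achieving all individualised treatment targets".
- **Outcome measures.** The determinant analysis stands in the same paragraph as the primary outcome, with SDM interactions for the same five factors. It is not listed among the secondary outcomes.
- **Statistical analyses.** The primary-outcome analysis "will be repeated with taken into account interaction of SDM with age, gender, education level, duration of diabetes and comorbidities". The general rule in the same paragraph is "A p-value of <0.05 is considered statistically significant". No separate level is given for the interactions. The text does not say whether the five enter one model or five.

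The Sample size section plans only for the main effect: "the intervention group will show an increase of this percentage until 30" per cent, "whereas in the treatment-as-before-group this percentage will stay at 10" per cent. The result is 65 per group including drop-out, and 73 per group after the clustering correction.

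**The concern.** The article ranks the question of who benefits alongside the primary comparison and answers it with five significance tests, but the trial was sized for one main effect with a low control rate. Each interaction has to be estimated by dividing six or seven control successes between levels of a factor. With so few events, three things can go wrong: a chance interaction is declared a determinant, a coefficient cannot be estimated, or a real modifier is missed.

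At stake is part of research question 1. A chance result could be reported as showing which patients should be offered the decision tool. The main comparison between the arms is not affected.

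**Working it through.** **Inputs from the article.** Success rates 10% and 30%, two-sided 0.05, 80% power, 10% drop-out, about 6 patients per practice, within-cluster correlation 0.025 (all Sample size); 40 practices (Abstract); five factors, relative risk and p<0.05 (Statistical analyses).

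**The plan's own figure.** Unpooled two-proportion formula: n = (1.96 + 0.8416)² × (0.09 + 0.21) / 0.20² = 58.9, so 59. With drop-out, 59 × 1.1 = 64.9, so 65. Design effect 1 + (6 − 1) × 0.025 = 1.125; 65 × 1.125 = 73.1, so 73. The stated 65 and 73 are reproduced.

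**Expected events.** 73 × 0.9 = 65.7 analysed per arm. Controls: 65.7 × 0.10 = 6.6. Intervention: 65.7 × 0.30 = 19.7. Total 26.3. With no drop-out: 7.3 + 21.9 = 29.2. If SDM had no effect: 2 × 6.6 = about 13.

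**Nominal false-positive chance.** Five independent tests at 0.05: 1 − 0.95⁵ = 22.6%. This does not depend on fitting the interactions jointly.

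**Power for one interaction.** Take a balanced two-level factor with 33 patients in each of four cells, a control rate of 10% in both halves, and relative risks of 2 and 4 (intervention rates 20% and 40%). Each cell contributes (1 − p)/(33p) to the variance of the log ratio of relative risks:

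- SE = √[(9 + 9 + 4 + 1.5)/33] = √(23.5/33) = 0.844
- ln 2 / 0.844 = 0.82
- power about 13%

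For 80% power, using the SE with no interaction, √[(9 + 9 + 2.33 + 2.33)/33] = 0.829, the ratio of relative risks would have to be exp(2.80 × 0.829), about 10.

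**Simulation with no true interaction.** The article gives no covariate distributions, so these were assumed: age and duration continuous; sex, education and comorbidity binary, with the prevalences shown for the last two. There were 20 practices per arm and a within-cluster correlation of 0.025. The model was a joint Poisson relative-risk model with cluster-robust SEs, with 3,000 trials per row.

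| Per arm | Comorbidity / education | Inestimable | At least one p<0.05, all trials | Same, among fitted | Either failure |
|---|---|---|---|---|---|
| 66 | 50% / 50% | 15% | 28% | 33% | 43% |
| 66 | 30% / 30% | 28% | 23% | 33% | 51% |
| 66 | 80% / 50% | 36% | 21% | 33% | 57% |
| 73 | 50% / 50% | 11% | 29% | 32% | 39% |
| 73 | 30% / 30% | 23% | 23% | 30% | 46% |
| 73 | 80% / 50% | 29% | 23% | 32% | 52% |

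A second set of clustered relative-risk runs gave 30-40% of joint fits with a nominally significant interaction, falling to 13-22% once runaway fits were discarded, and 15-45% runaway or inestimable fits. One interaction per model gave the same 15-45% and no fewer false positives. Logistic models gave 19-22% false positives among fitted models and 13-38% inestimable.

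**The case against.** Much of the case on the other side is sound.

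- **A condensed article may leave detail to an analysis plan.** An exploratory label or multiplicity rule may stand in a document not shown, so its absence alone is no fault. What remains is what the article itself fixes: the rank of the question, the five factors, the general threshold, and a sample size for the main effect only.
- **Joint fitting is an inference.** A reader might take the text to mean one model with at least 12 coefficients and about two events for each. The article does not say so. The point does not need that reading, because the nominal 23% and the low power apply either way.
- **Failure is not shown to be likely.** A reader might infer that a false determinant or an unusable model is the probable outcome. Neither passes one half on its own in any of the runs, and the two combined do so only under some assumed distributions. Some significant interactions would also come from visibly runaway fits that an analyst would reject.
- **Diabetes duration.** A reader might infer that duration is confined to a four-year band and should be dropped, since Practices and patients admits the non-ADDITION patients "known with type 2 diabetes for 8-12 years but not diagnosed in the ADDITION study". The Abstract gives 8-15 years. The two statements conflict, and a narrow range lowers power without making the factor an error.
- **Separate models.** A reader might expect one interaction per model to be the cure. In the simulations it gained nothing.

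It also counts in the plan's favour that the five modifiers are named in advance, and low interaction power is common in trials sized for a main effect. This limits the weight of the point but does not remove it, because few such trials put the search inside their first research question.

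**Conclusion.** The concern holds in limited form. On the design rates the trial expects about 26 successes, 6 to 7 of them in controls. Five interaction tests at 0.05 then carry a nominal 23% chance of at least one false determinant (roughly 20-40% in simulated relative-risk models), an 11-45% chance of an inestimable or runaway coefficient, and about 13% power for relative risks of 2 versus 4 in equal halves.

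The event counts rest on the article's planning rates and drop-out. The 23% assumes five independent single tests. The simulated ranges rest on assumed covariate distributions and on the choice of model, and should be read as ranges. The conclusion that the analysis cannot reliably identify who benefits does not depend on any one of these choices. The primary comparison and the sample size for it stand.

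**What to change.** In the research questions (Background), Outcome measures and Statistical analyses:

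1. State that the SDM interaction analysis is exploratory.
2. Report each interaction as a ratio of relative risks, or a difference in risk differences, with its 95% confidence interval.
3. Exempt these analyses from the general p<0.05 rule.
4. Limit the determinants part of question 1 to description.

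If a separate analysis plan exists, its wording should match. Nothing here requires one interaction per model or the removal of diabetes duration, although the two stated duration ranges should be reconciled.

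The cost is a few sentences, with no extra patients, data or change to the primary analysis. The trial gives up a confirmatory statement about who benefits from SDM, which about 26 events could not support.

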Participants in both groups will be asked to complete and return the following questionnaires baseline and after 24 months at home.the Diabetes Treatment Satisfaction Questionnaire (DTSQ) [30] which includes 8 items; scores range from 0 (very dissatisfied) to 6 (very satisfied), totally from 0 to 48. The DTSQ is reliable, valid and sensitive to change in diabetes patients [30];the Audit of Diabetes Dependent Quality of Life (ADD QoL-19), which measures the perceived impact of diabetes on the quality of life; it includes 19 items, ranging from -3 to 3 on different questions, with 0 as the neutral score. Scores below 0 reflect a negative influence of the item on quality of life, and all above 0 reflect positive influences. The impact scores are weighted (impact rating x importance rating), so the actual scores per item can range from -9 to 9. The ADDQoL-19 has good psychometric properties and provides clinicians and researchers with a useful tool for comprehensively assessing quality of life in adults with T2DM [31];the Well-Being Questionnaire (W-BQ12) that consists of 12-items in three 4-item subscales: negative well-being (item 1-4, higher score reflects a greater sense of negative well-being), energy (items 6 and 7 are reversed, and then together with 5 and 8 form the total amount of energy) and positive well-being (items 9-12, the higher the score the greater the sense of positive well-being). The total score ranges from 0 to 36 and is called the general well-being score. Higher scores indicate a higher overall sense of well-being [32];the European Quality of Life (EQ-5D) questionnaire, that covers 5 dimensions (mobility, self-care, usual activities, pain/discomfort and anxiety/depression) and a Visual Analogue Scale (VAS) where respondents can rate their health. Item scores range from 1-3, and a 5-digit health profile is formed, placing the 5 numbers behind each other. It is a well-validated, reliable and responsive instrument for health measurement in patients with a wide range of medical conditions. Values found in the UK have been validated for the Netherlands [33-35];the Short Form-36, a validated 36-item instrument for the self-evaluation of health status with eight subscales: Physical Functioning (10 items), Role Physical (4 items), Bodily Pain (2 items), General Health (5 items), Vitality (4 items), Social Functioning (2 items), Role-Emotional (3 items) and Mental Health (5 items). These scales can be summarised in Physical Health and Mental Health. The 36 items differ in the scoring ranges. The Dutch version has proved to be a practical, reliable and valid instrument [36,37];the Diabetes Coping Measurement Questionnaire (DCMQ), consisting of 21 items in 4 subscales: spirit coping, avoidance coping, passive resignation coping and diabetes integration coping. Overall scores range from 7 to 35. The items are measures on a 5-point Likert scale, ranging from 1 (“disagree”) to 5 (“agree strongly”) or the other way around from 1 (‘I strongly agree’) to 5 (I ‘disagree’). Higher scores on tackling spirit and diabetes integration indicate more adaptive coping. Higher scores on passive resignation and avoidance indicate poor coping [38].

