
A process evaluation of the shared decision making ability of the general practitioners will be measured in the intervention group at baseline and after 12 months, and in both treatment groups at 24 months. Both the patients and GPs will be asked to complete The Shared Decision Making Questionnaire, both the patient (SDM-Q9-patient) and GP (SDM-Q9-doc) version will be used to evaluate this process.

The Shared Decision Making Questionnaire (both SDM-Q9 versions) [39-41] includes 9 items with ratings from 0 (completely disagree) to 6 (completely agree); the total score ranges from 0 to 54. It is a continuous scale, and the questionnaire developers did not describe any thresholds for ‘bad’ or ‘good’ SDM. Over the last years the SDM-Q9 has become a frequently used instrument in clinical practice. It has been translated into several languages. Internal consistency has been assessed for the Spanish and Dutch version (Rodenburg-Vandenbussche S, Pieterse AH, Kroonenberg PM, Stiggelbout AM,et al.: Further validation of the SDM-Q-9 and SDM-Q-Doc: psychometric properties in Dutch patients from primary and secondary care. Submitted). Item discrimination parameters were above 0.4 for all but one item. An analysis of internal consistency yielded a Cronbach’s α of 0.88 [39]. The Dutch version is currently being validated [41]. A modified version of the Control Preferences Scale (CPS) is used to determine the experienced role of decision making of the GP and patient. The CPS measures at a 5-point Likert scale, and has shown good reliability and validity [41,42]. The original Control Preference Scale by Degner [41], was developed to measure preference for involvement and is one of the most commonly used instruments to assess preferred decisional role [41,42].

Subsequently, the GPs of both groups (the intervention group trained, the control group not) will audio- or videotape one of their yearly consultations with a T2DM patient. They can choose the consultation to be taped themselves. These tapes will be evaluated by two independent observers, making use of the SDM-Q9, to assess the extent to which the GP is likely to involve his/her patients in the diabetes treatment.

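### For five patient-reported domains the plan, as naturally read, compares arms on change from baseline without adjusting for the baseline score, which loses precision and lets chance imbalance move the estimate

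*Protocol article*

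**What the plan says.** The Outcome measures section lists as secondary outcomes "diabetes treatment satisfaction, perceived quality of life, health status, well-being, and coping style". Under Measurements, data collection, the schedule for these scales is: "Participants in both groups will be asked to complete and return the following questionnaires baseline and after 24 months at home". Both arms therefore supply one baseline and one 24-month score per patient.

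Under Statistical analyses, within- and between-group differences in these five domains "between baseline and 24 months follow-up will be analysed by using paired t-tests and mixed models respectively": paired t-tests within groups, mixed models between groups. The section adds: "We will add random effects for patient and practice". It does not say how the baseline score enters the between-group model, whether as a covariate, as an outcome with the arm means left free, or as an outcome with the arm means set equal.

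The SDM-Q9 is treated differently. The process evaluation "will be measured in the intervention group at baseline and after 12 months, and in both treatment groups at 24 months", so controls have no baseline value, and the between-arm analysis is at the endpoint: "Mixed models will be used to study the between groups differences after 24 months".

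**The concern.** The quantity named for the between-group comparison is the difference from baseline to 24 months, the same quantity that the paired t-test uses within groups. A patient random effect needs more than one score per patient, which suggests that both scores enter as outcomes. The neighbouring SDM-Q9 paragraph shows that the authors word an endpoint comparison differently when they intend one. Together these point to a difference in change.

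A change score subtracts the whole baseline value although the two scores correlate below 1, so baseline noise enters the treatment contrast. Baseline adjustment uses the same data and subtracts only the predictive part.

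This matters because the second research question (Background) rests on these contrasts, and the Sample size section provides only for the binary primary outcome. Randomisation is by practice without stratification, so some chance baseline difference on one or more scales is to be expected.

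**Working it through.** **Inputs from the protocol article.** 73 patients per group, intracluster correlation (ICC) 0.025, about 6 eligible patients per practice, drop-out 10% (Sample size); 40 practices (Abstract); no stratification (Randomisation).

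**Assumptions.** The baseline to 24-month correlation rho is not given and is varied from 0.3 to 0.8. Score SDs are taken as equal at both times. The planning ICC is borrowed for these scales. All effects are in SD units.

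**The plan's own figure.** For 10% versus 30%, two-sided 5%, 80% power and unpooled variance: (1.960 + 0.842)² × (0.09 + 0.21) / 0.20² = 58.9, so 59; 59 × 1.1 = 65; design effect 1 + 5 × 0.025 = 1.125; 65 × 1.125 = 73. The stated 65 and 73 reproduce. They concern the primary outcome; there is no figure for the patient-reported scales.

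**Precision.** Per patient, the variance is proportional to 2(1 − rho) for change and to 1 − rho² after baseline adjustment. The ratio of interval widths, change to adjusted, is √(2/(1 + rho)):

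| rho | width ratio | power of change analysis where adjusted has 80% |
|---|---|---|
| 0.3 | 1.24 | 62% |
| 0.5 | 1.15 | 68% |
| 0.7 | 1.08 | 73% |
| 0.8 | 1.05 | 76% |

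At rho 0.5, with 73 per group and design effect 1.125 applied to both analyses, the 95% half-width is 1.96 × √(2 × 0.5 × 2/73 × 1.125) = 0.344 SD for change and 1.96 × √(0.75 × 2/73 × 1.125) = 0.298 SD adjusted.

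**Imbalance.** With 73/20 = 3.65 patients per practice, the standard error of the baseline difference is √(2 × (1 + 2.65 × 0.025)/73) = 0.171 SD. An imbalance above 0.25 SD on a given scale then has about a 14% chance. Given an imbalance d, the change contrast moves by −(1 − rho) × d. For d = 0.25 SD this is 0.125 SD at rho 0.5 and 0.075 SD at rho 0.7, with no true effect, in favour of the arm that started worse.

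**Does the mixed model behave this way?** In 150 simulated cluster trials (rho 0.5, 40 practices of 4 patients, complete data, patient and practice random effects):

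| analysis | empirical SD of estimate | slope on baseline imbalance |
|---|---|---|
| mixed model with time, arm and arm-by-time | 0.162 | −0.49 |
| mixed model with common baseline mean | 0.141 | −0.03 |
| 24-month score adjusted for baseline | 0.142 | 0.02 |

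The first model reproduced the raw change-score difference to within rounding error, and its slope is close to the theoretical −0.50. The SD ratio is 0.162/0.142 = 1.14, close to the 1.15 in the formula.

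**The case against.** The strongest reply is that the plan never says change score. It gives no fixed effects, and a mixed model with a common baseline mean fits the same words and has the precision of baseline adjustment. On that view this is only an unstated detail of a secondary analysis, which an article may leave to a fuller document. The first part stands: change from baseline is the natural reading, not an explicit statement. The second does not dispose of the point, because the article does name the quantity compared between arms, and the wording as it stands leads an analyst to the less precise contrast.

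Two stronger readings should be resisted. A reader might infer that every patient-reported outcome is affected. The patient-completed SDM-Q9 is not, since it is compared at 24 months. A reader might also infer that the analysis is biased or inflates false positives. Over randomisations the change contrast is unbiased, and its standard error already includes chance baseline variation, so the nominal error rate holds. The distortion is conditional on the imbalance that occurs, and 0.125 SD lies well inside a half-width of 0.344 SD.

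The remaining objections hold in part. The size depends on a correlation that the article does not give; at 0.8 the loss is small. With drop-out, the mixed model can keep patients with one score, and its contrast then no longer equals the change-score difference exactly. Baseline adjustment also has a small cost, set out with the remedy.

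**Conclusion.** The point holds for the five domains, as a loss of efficiency and a conditional sensitivity to imbalance. If baseline means are left free, intervals are about 5% to 24% wider than they need be for rho from 0.8 to 0.3. Where the adjusted analysis would have 80% power, the change analysis has between 76% and 62%. These figures rest on the assumed rho, equal SDs, complete pairs and the same design effect in both analyses. The result does not support calling the planned analysis invalid, and it has no bearing on the primary outcome. The change is worth making because the baseline scores are already collected in both arms.

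**What to change.** State in the Statistical analyses section that, for the five domains, the between-arm estimate is the difference in the 24-month score, with the patient's own baseline score as covariate, arm as factor and a practice random effect. Alternatively, to keep patients with only one score, specify a longitudinal mixed model of both scores with a common baseline mean in the two arms and random effects for patient and practice. The within-group paired t-tests can stay as description.

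The cost is one sentence and no new data. The covariate version drops patients without a baseline score unless it is imputed. The common-mean version assumes equal baseline means under randomisation. The article does not say whether practices included their patients before or after allocation, so the choice should be made with that order in view.
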